Advanced diabetes technologies such as continuous glucose monitoring (CGM) may lessen the burden of diabetes self-management by providing real-time glucose values, alerting adolescents and caregivers to low and high blood glucose levels, and indicating the predicted direction of blood glucose levels in the next hour [20,21]. As of 2023, nearly 80% of adolescents with T1D use CGM [1]; however, the average HbA_1c_ among CGM users in this age group remains above the recommended level [22], suggesting that CGM alone is not enough for youth to meet HbA_1c_ targets.

While adolescents who regularly use CGM report high levels of satisfaction and quality of life [23], they also report concerns about device visibility, feeling “spied on,” alarm and device fatigue, feeling as though device data are unreliable or untrustworthy, and being overwhelmed by constant streams of data [24]. The emotional, social, and practical burden of CGM can contribute to distress, reduced motivation for device engagement, and, ultimately, lower device adherence [25]. Fewer than 30% of individuals with T1D report using any real-time CGM features such as event logging or data sharing, and less than 75% have customized their high and low alert thresholds [26]. While reviewing CGM data may support problem-solving and decision-making among adolescents with T1D [27,28], fewer than 20% of adolescents review their diabetes device data independently [23]. Additional research is needed to understand how adolescents are leveraging (or not leveraging) diabetes devices for self-management decisions in daily life, and how the use of diabetes devices impacts their overall health and well-being. Understanding how adolescents use their devices can help health care teams and families to identify key barriers to self-management and support young people to optimize self-management and care.

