Beginning after the baseline survey is completed, participants will receive SMS text messaging survey invitations 4 times per day on a fixed schedule in the morning (10 AM), afternoon (2 PM), early evening (6 PM), and end-of-day (10 PM) [3] The morning, afternoon, and early evening surveys focus on interactions with their diabetes technology, challenges in managing diabetes, and other events that have occurred in the last few hours. For example, 1 question asks, “What have you been doing in the last few hours (ie, exercising, eating, at school, etc)?” In the evenings (10 PM), participants will complete a guided reflection using open-ended questions. During the reflection, they will be asked to open their diabetes device app and review the graph of their glucose levels throughout the day. Qualitative and quantitative data will be integrated during data collection as participants provide written reflections on their CGM data in daily SMS text messaging surveys. In addition, they will share information about what activities they did that day and how they feel events and activities impacted their diabetes. For example, the first question asks, “Overall, how did you feel about your diabetes today?” Sample daily and end-of-day survey question items and their alignment with the COM-B model can be found in Table 1. Complete daily and end-of-day SMS text messaging surveys are included in Multimedia Appendix 3. Participant response rates will be tracked automatically by REDCap throughout the study. In addition, participants will complete an open-ended text messaging survey after the 30 days of daily surveys are completed to qualitatively share their study experiences, burden, and study acceptability.

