During the same 30 days, participants will be asked to continue CGM as prescribed to collect glucose levels. Depending on the device manufacturer, glucose levels are measured automatically every 1 to 15 minutes. By not introducing a new device, reactivity is reduced, and we are able to capture typical self-management behaviors and glycemic levels in this population. Likewise, participants do not have to learn to use a different device solely for the purpose of this study. Glycemic data are not blinded from participants to maintain normalcy with their daily routine and to maintain their safety in managing potentially dangerous high and low glucose levels during the study period. After completion of the daily survey portion of the study, participants will receive a secure REDCap survey link to share their CGM data from the previous 30 days downloaded as a .csv file from their CGM platform (eg, Dexcom Clarity). In addition, participants will be asked to reflect on the feasibility and acceptability of the study through 7 survey questions. Questions include study barriers, facilitators, and reflections on the length and timing of data collection (see Multimedia Appendix 4 for full closeout survey).

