To test for mean differences in psychosocial and behavioral characteristics between glycemic level groups (HbA_1c_>9% and those with HbA_1c_≤9%) at baseline, 1-tailed *t* tests will be used. If the data are nonparametric, appropriate alternative tests (ie, the Wilcoxon rank paired test) will be performed. For all participants with at least 28 days of continuous glucose data, we will use linear mixed models to identify risk factors that influence blood glucose levels, model changes in blood glucose over time, and test any intervention effect resulting from longitudinal data collection. Additional statistical tests may be performed as appropriate based on the data collected. Statistical analysis will be performed on the data of all included study participants, and a statistical significance level of 5% (α=.05) will be used to test for differences and associations.

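### The planned test of an intervention effect of the data collection has no unexposed CGM days, so a change in glucose level that starts with the surveys cannot be estimated

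*Protocol article*

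**What the plan says.** All of the following is in the protocol article.

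- **The test.** Quantitative Analysis: "For all participants with at least 28 days of continuous glucose data, we will use linear mixed models". One stated use of these models is to "test any intervention effect resulting from longitudinal data collection". No contrast defining that effect is given.
- **The exposure.** Real-Time Daily Data Collection: "Beginning after the baseline survey is completed, participants will receive SMS text messaging survey invitations 4 times per day". In the 10 PM survey "they will be asked to open their diabetes device app and review the graph of their glucose levels throughout the day".
- **The glucose window.** Same section: "During the same 30 days, participants will be asked to continue CGM as prescribed to collect glucose levels". After the survey portion ends, participants are asked to "share their CGM data from the previous 30 days downloaded as a .csv file from their CGM platform".
- **The claim about reactivity.** Same section: "By not introducing a new device, reactivity is reduced, and we are able to capture typical self-management behaviors and glycemic levels in this population".
- **Background.** Introduction: "fewer than 20% of adolescents review their diabetes device data independently".

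There is one cohort of 30 to 40, and everyone receives the surveys. Eligibility (Recruitment and Sampling) requires at least 6 months of CGM use and use on at least 20 days per month. HbA1c appears only as a recent or baseline value from records. No follow-up HbA1c is described.

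**The concern.** The study prompts every participant, every night, to do something that the Introduction says most adolescents do not do on their own. An effect of the study procedures on glucose is therefore plausible, and the authors are right to want to look for one. Estimating it needs glucose readings with and without the procedures, and the plan collects only readings with them.

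Two statements are at stake. The first is the statement that typical behaviours and glycaemic levels are captured. It is justified by not introducing a new device, which does not address the prompted nightly review. The second is the Discussion's open question about the impact of data collection on participant behaviour, on which the mixed model would be the only glucose-based evidence.

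**Working it through.** The article gives no power, effect size or standard deviation for this test, so there is no stated figure to reproduce. The core of the point needs only the design.

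**1. Identifiability.** Let exposure be 1 on a survey day and 0 otherwise. With CGM days 1 to 30, all survey days, exposure is 1 in every row. The fixed-effect matrix (intercept, day, exposure) has 3 columns and rank 2, because exposure duplicates the intercept. The level effect has no estimate, whatever random effects or covariance structure are chosen.

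**2. What remains: the day trend.** An illustrative simulation was run with assumptions that are not in the article: 35 participants, mean glucose 180 mg/dL, between-person SD 40, day-to-day SD 30, SD of individual slopes 0.5 mg/dL per day, two-sided alpha 0.05, 2,000 runs. The 30-day slope test rejects as follows:

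| Truth | Rejection rate |
|---|---|
| No effect, no drift | 5.7% |
| Immediate sustained drop of 10 mg/dL, no drift | 4.8% |
| No effect, background drift +0.3 mg/dL per day | 57% |
| Survey slope -0.3 offset by background drift +0.3 | 5.0% |

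The second row follows by construction, since a flat step has zero slope within the window. The third and fourth rows show that the trend cannot separate a survey effect from drift.

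**3. Where the trend does work.** Take time in range with an assumed within-person daily SD of 15 points, independent days, and an effect falling linearly from +5 points to 0 over the 30 days. The slope is 5/29 = 0.172 per day in size. The sum of squared day deviations is 2,247.5, so the per-person slope SD is 15/√2,247.5 = 0.316. For n = 30 the SE is 0.316/√30 = 0.058 and the ratio is about 3.0, giving power of about 82% (92% for n = 40). This requires no other time trend.

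**4. Adding pre-survey days.** With 14 pre-survey days (days -13 to 0), a design with intercept, day, period and period-by-day has 4 columns and rank 4, so both a level change and a slope change are estimable.

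**5. Why a simple during-minus-before difference is not enough.** Under the assumptions of step 2 it detects a 10 mg/dL drop in about 98% of runs. It also rejects in about 76% of runs under drift alone: the mean days of the two periods are 15.5 and -6.5, so a drift of 0.3 per day shifts the difference by 22 × 0.3 = 6.6 mg/dL.

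**6. Precision of the segmented level change.** Per person, the variance at survey start (day 0) is SD² × [(1/n₁ + m₁²/S₁) + (1/n₀ + m₀²/S₀)], where n is the number of days, m the mean day and S the sum of squared day deviations (1 = during, 0 = before).
- During: 1/30 + 15.5²/2,247.5 = 0.140.
- 14 days before: 1/14 + 6.5²/227.5 = 0.257. Total 0.397.
- 30 days before: 1/30 + 14.5²/2,247.5 = 0.127. Total 0.267.

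With SD 30 and 35 participants, the SE is 30 × √(0.397/35) = 3.2 mg/dL for 14 days and 30 × √(0.267/35) = 2.6 for 30 days. The 95% half-widths (t = 2.03) are about 6.5 and 5.3 mg/dL. These assume independent days and the same level change in everyone, so they are optimistic.

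**The case against.** Several counter-arguments deserve weight.

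- **A reader might infer that no effect of the procedures can be detected at all.** That is too broad. Step 3 of the working shows that a fading effect can be detected with good power if nothing else is trending. The article does not say which form reactivity would take, so it does not support calling an immediate sustained effect the most likely one.
- **A reader might infer that a null trend will be reported as absence of reactivity.** The article does not say so. It says only that reactivity is reduced, and the Discussion assigns the question to feasibility and acceptability findings. The interview asks directly about behaviour change. These are self-reports, however, and supply no unexposed glucose data.
- **Exposure is not strictly constant,** because survey completion is expected to be near 70%. A contrast by completion is conceivable, but the article does not propose it, and completion is self-selected and probably tied to engagement and glycaemia.
- **The model details may sit in an unseen analysis plan.** The contrast may, but no analysis plan can recover days that the described upload does not request.
- **A late upload could shift the 30-day window.** Read with the sentence on the same 30 days, the request most naturally means the survey window, and the closeout survey is in an appendix not shown. This is not a separate fault, and fixed dates settle it anyway.
- **The test is a small part of a grounded-theory study,** whose sample size rests on qualitative sufficiency. This stands and limits the severity.

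**Conclusion.** The point holds in a limited form. As described, the study cannot estimate a change in glucose level that begins with the surveys, because every planned CGM day is a survey day. This follows from the design alone. The remaining day trend has zero expected slope under an immediate sustained effect, and can be read as a gradual or fading effect only on the unstated assumption of no other time trend. The rejection rates and interval widths rest on assumed variances and drifts and are illustrative.

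Severity is moderate. Neither aim depends on this test, but a named test that cannot estimate a main form of its target should not stand as written.

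**What to change.** **Preferred.** Replace the closeout request for the previous 30 days with fixed calendar dates for each participant: from at least 14, preferably 30, days before the first SMS survey through the last survey day. The readings should exist, given the required 6 months of CGM use. Fit a segmented mixed model with the pre-survey trend and with level and slope changes at survey start. State how the 28-day data requirement applies to each period, since eligibility guarantees only 20 days of use per month. Report the result as an uncontrolled interrupted time series, because there is still no concurrent comparison.

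**Cost.** A minor ethics and consent change, a longer date range in the same file, and a re-export request to those already enrolled. There were 25 by December 2025, so only about 5 to 15 of the planned 30 to 40 remain to be reached prospectively. The result therefore depends largely on re-exports, and the article does not say how long the CGM platforms keep data.

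**If pre-survey data cannot be obtained.** Delete the intervention-effect test, report a descriptive within-study time trend, and qualify the statement that typical behaviours and glycaemic levels are captured. This needs no new data.

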#### Mixed Methods Integration

Mixed methods findings will help us to better understand how diabetes devices are used for daily T1D self-management among adolescents with T1D and how psychosocial factors and daily self-management behaviors are related. Aligned with the longitudinal, convergent mixed methods design, integration of qualitative and quantitative approaches will occur through sampling, data collection, analysis, and interpretation [68,69]. For example, integration occurs during sampling by collecting data from identical samples in the qualitative and quantitative approaches. During data collection, participants will provide written reflections through SMS text messaging surveys (qualitative) on their glucose data from each day (quantitative). In addition, interview participants will provide narratives of their self-management behaviors that can be compared to CGM metrics.

During mixed methods analysis, we will first create participant summaries that include individual-level responses from interview transcripts, daily SMS text messaging surveys, baseline surveys, and CGM data. Raw and summary level baseline survey responses and summary level CGM metrics will be imported into the qualitative analysis software alongside the coded qualitative data. In addition, ambulatory glucose profiles from CGM data will be imported to provide context of recent and current glucose levels coinciding with real-time survey responses. We will then merge all data sources to create written participant summaries. Example participant profile provided in Multimedia Appendix 5.

We will also merge results to compare qualitative findings to diabetes outcomes (eg, self-management behaviors and diabetes distress) and glycemic levels. Using mixed methods features of MAXQDA software, we will create crosstabs to allow for comparison of qualitative findings by quantitative measures. For example, qualitative findings from interviews and daily SMS text messaging surveys will be compared between those with HbA_1c_ of more than 9% and those with HbA_1c_ of 9% or less. Integration through merging will allow us to identify patterns that can help to explain variation in glycemic levels or other diabetes-related physical and mental health outcomes. A similar approach will be used to integrate feasibility and acceptability data collected through the closeout survey and follow-up interview. Meta-inferences will be created to explain study feasibility and acceptability, including the perceived burden of participating in real-time and longitudinal data collection.

We will also create visual joint displays [69,70] that compare qualitative and quantitative results to generate meta-inferences. For example, one such joint display will examine patterns in qualitative findings by different glycemic outcomes to determine differences in the daily experiences of youth that help to explain glycemic levels and variability. A similar joint display can array qualitative findings by baseline measures of self-reported diabetes distress and self-management behaviors. Integrated findings will be used to further refine our theory of self-management with diabetes devices in this population.

When merging qualitative and quantitative results, we will determine whether the findings are concordant across approaches. Concordant results will be discussed among the research team, returning to the emergent grounded theory and comparing data and analytical categories (in qualitative findings) to quantitative results to examine meta-inferences. Both concordant and discordant results can support the refinement of the theory and generate additional hypotheses for future research [71-73].

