## Methods

### Overview

This longitudinal, convergent mixed methods study leverages a real-time approach to develop a theory of self-management among adolescents with T1D who use CGM. We will conduct a grounded theory analysis to describe self-management in this population, which will inform future intervention development. We aim to enroll approximately 30 to 40 adolescents with T1D who already use CGM to complete 30 days of real-time, narrative data collection via SMS text messaging and 30 days of CGM. Additional data will be collected via a baseline survey and one-time follow-up interview to further develop the theory.

When applied to diabetes, real-time data collection (eg, ecological momentary assessment) can allow us to more accurately assess T1D self-management beliefs, behaviors, and event experiences, reduce recall bias, help researchers to understand behaviors in context, and support the development of timely and tailored interventions [29-32]. With the growth of CGM among adolescents, continuous and real-time glucose data have been incorporated into momentary assessments [1,33] While real-time quantitative assessments help to characterize important variations that influence self-management, the broader context of an individual’s experience during those moments remains poorly understood. A mixed methods approach blending real-time and contextual data could address these gaps to provide a more comprehensive understanding of adolescents’ experiences and identify potential intervention targets and strategies. In this study, we will use a qualitative real-time approach to further explore the lived experience of T1D self-management from the perspectives of adolescents using diabetes technology.

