### Recruitment and Sampling

A list of patients with T1D, aged 12 to 18 years, who (1) use CGM, (2) received care in the U-M Pediatric Diabetes Clinic in the past 12 months, and (3) have at least 1 HbA_1c_ laboratory result from the past 12 months will be generated using DataDirect (University of Michigan Medical School) and Electronic Medical Record Search Engine (EMERSE) [40]—university-developed tools for performing systematic searches of structured and unstructured patient medical records [41]. The list will include basic demographic, clinical, and contact information for identified patients.

Consistent with a grounded theory approach, we will use theoretical sampling to help ensure that adequate data are collected to address our research aims. For our initial sampling strategy (a priori) [42], we seek to enroll participants with diverse diabetes outcomes and experiences. We will intentionally recruit and enroll participants with HbA_1c_ of 9% or less and more than 9% to ensure adolescents with low and high glycemic levels are represented. We aim to recruit and enroll approximately equal groups with high and low glycemic levels. A purposive sampling approach will also be leveraged using demographic and clinical factors including age, gender, years since diagnosis, and other social determinants of health (eg, family income and food insecurity measures) to create a sample with varied experiences and backgrounds. Sociodemographic backgrounds that are under-represented within the clinical population (ie, Hispanic or Latino) in the sample will be intentionally oversampled. As data collection and analysis proceed, recruitment and sampling strategies may shift to explore variation in participant responses, develop relationships between codes and categories, and add details to the descriptions and characteristics of categories in the analysis [42].

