### Semistructured Interview

A subsample of participants (n=20‐30) will be invited to complete a 1-hour follow-up interview with a member of the study team trained in qualitative data collection and analysis. A maximum variation sampling approach will be leveraged and rely on recent HbA_1c_ levels, baseline survey scores, age, gender, race or ethnicity, diabetes duration, and diabetes device use as well as responses to the SMS text messaging surveys. Interviews are intended to further explore their approach to self-management using their diabetes devices. Interview prompts will focus on the participants’ daily approach to managing their diabetes, including decision-making, problem-solving, and interactions with technology. Alignment of interview prompts with the COM-B model is described in Table 1. Likewise, a portion of the interview will be dedicated to exploring study feasibility and acceptability, including perceived study burden and experiences of behavior change during the study period. Interviews will be conducted using Health Insurance Portability and Accountability Act (HIPAA)-compliant web conference tools (eg, Zoom; Zoom Communication, Inc), audio-video recorded, and transcribed for analysis. In line with a traditional qualitative approach, analysis and data collection will be completed simultaneously, and the final sample size will be determined by theoretical saturation.

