## Results

This study was reviewed and approved by the institutional review board in January 2025 and enrolled its first participant in April 2025. As of December 2025, 25 participants have enrolled in this study, and we anticipate meeting our enrollment goal of approximately 30 to 40 participants in early 2026. We anticipate findings to become available in the following several years through conference presentations and peer-reviewed publications. Furthermore, findings will inform the development of an intervention to address diabetes self-management and decision-making in adolescents with T1D.

Few previous applications of real-time data collection have leveraged conversational SMS text messaging (where questions are sent one-at-a-time following participant responses), and, as such, there is little data on participant burden and compliance available for this method; however, early studies using closed-ended surveys indicate high satisfaction and compliance rates (≤95%) among adolescents and young adults [74], especially when fewer prompts were used [75,76]. As a result, our study incorporated several recommendations for burden reduction and compliance optimization such as working with a population that feels connected to our study objective, using shorter, less frequent prompts, allowing a window of 2+ hours for responses, allowing the use of participants’ own devices, providing a monetary incentive after completing the study, and co-developing surveys with youth with lived experience of T1D from the T1DYAC [77,78]. As a result, we are hopeful for response rates of at least 70% in this study. Likewise, we expect themes emerging from the analysis of feasibility and acceptability responses to highlight overall participant satisfaction and low burden.

We anticipate that sensor use time will be above 75%, as this population will already use CGM prior to study enrollment. In addition, we anticipate that participants with HbA_1c_ of more than 9% will report lower problem-solving, self-management behaviors, and diabetes device use, and higher diabetes distress and depression compared with those with HbA_1c_ of 9% or less.

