Primary qualitative outcomes include thematic description of typical and momentary behaviors and responses to diabetes distress, problem-solving, and decision-making. Historically, reported adherence levels to real-time data collection (eg, quantitative ecological momentary assessment) among children and adolescents have been high (78%), including among youth using mobile devices and wearables (73%) [79]. We anticipate that, even with up to 30% missing data on daily surveys, the combined repeated surveys and in-depth interviews will provide a sufficient sample size to detect differences between adolescents with HbA_1c_ of 9% or less and more than 9%. However, monetary incentives are provided based upon the completion of the study and prorated based on the level of completion to incentivize data completeness. We anticipate that theoretical saturation will likely occur prior to the enrollment of 40 participants. When integrated, the quantitative and qualitative data sources will provide novel insights into daily self-management behaviors for adolescents with T1D.

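### Repeated surveys and interviews are counted as sample size for the HbA1c comparison, and the crosstabs that make it state neither a unit nor an adjustment for text volume

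*Protocol article*

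**What the plan says.** The sampling plan fixes the number of adolescents and their split: "We aim to enroll approximately 30 to 40 adolescents with T1D who already use CGM" (Overview) and "We aim to recruit and enroll approximately equal groups with high and low glycemic levels" (Recruitment and Sampling). Each adolescent is to "complete 30 days of real-time, narrative data collection via SMS text messaging" (Overview), and "participants will receive SMS text messaging survey invitations 4 times per day on a fixed schedule" (Real-Time Daily Data Collection).

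For interviews, a subsample of 20 to 30 "will be invited to complete a 1-hour follow-up interview" (Semistructured Interview). The Data Collection Procedures section calls the interview optional.

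In Mixed Methods Integration, "we will create crosstabs to allow for comparison of qualitative findings by quantitative measures". The worked example compares findings from interviews and daily texts between HbA1c above 9% and 9% or less. The section does not say whether a cell counts participants, surveys or coded segments.

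The Results section says "we are hopeful for response rates of at least 70% in this study". It then says that, with up to 30% of daily survey data missing, "the combined repeated surveys and in-depth interviews will provide a sufficient sample size to detect differences between adolescents" in the two HbA1c groups.

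**The concern.** There are two linked problems.

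First, the Results sentence takes the number of surveys and interviews as the sample size for a contrast between HbA1c groups. Each adolescent belongs to one group throughout, so a further survey from the same person does not add a further member to either group. Read literally, the sentence promises far more resolution between groups than 30 to 40 participants can give.

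Second, the crosstabs are where that contrast would be made, and the article gives no denominator for them. Participants will contribute different amounts of text, and some will have a transcript while others will not. If text volume differs by HbA1c group, a theme can look more common in one group only because that group wrote or spoke more. A few prolific responders can also dominate a cell. These comparisons feed the joint displays and the refinement of the theory, so the distortion matters even if nothing is tested.

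**Working it through.** The document gives no effect size, power or sample-size calculation for the HbA1c comparison. The 30 to 40 rests on qualitative data sufficiency (Recruitment and Sampling), so there is no figure to reproduce.

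**Inputs from the protocol article**
- Participants: 30 to 40 in about equal groups, so 15 to 20 per group.
- Surveys: 4 per day × 30 days = 120 per participant at most.
- Response: 70% expected, so 120 × 0.70 = 84 answered per participant.
- Interviews: 20 to 30 participants (for example 20/40 = 50% or 30/40 = 75%).

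**Assumptions (not in the document)**
- Response rates by HbA1c group.
- Within-person correlation (ICC) of a code across surveys.

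**Step 1. Records against independent units.** Prompts number 30 × 120 = 3,600 to 40 × 120 = 4,800. At 70% that is 2,520 to 3,360 answered surveys, all from 30 to 40 people.

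**Step 2. Detectable difference with the participant as unit.** Two-sided 5%, 80% power, normal approximation: d = (1.960 + 0.842) × √(2/n).
- n = 15: 2.802 × 0.365 = 1.02.
- n = 20: 2.802 × 0.316 = 0.89.

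The unit is the SD of participant-level values. One-sided, the results are 0.91 and 0.79. For a theme held by 20% of participants in one group, the other group must reach about 69% (n = 15) or 63% (n = 20), two-sided.

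**Step 3. The same formula with surveys as units.** Units per group are 15 × 84 = 1,260 or 20 × 84 = 1,680, so d = 0.11 or 0.10, in SDs of a single survey. This is a different SD from Step 2, so the figures need a common scale. The design effect is 1 + 83 × ICC, and the survey-level d must be multiplied by its square root:

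| ICC | Design effect | Factor | d in survey SDs, n = 15 / 20 |
|---|---|---|---|
| 0.05 | 5.15 | 2.27 | 0.25 / 0.22 |
| 0.10 | 9.3 | 3.05 | 0.34 / 0.29 |
| 0.50 | 42.5 | 6.52 | 0.73 / 0.63 |

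Counting surveys therefore understates the detectable difference about 2- to 6.5-fold over this range.

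**Step 4. Volume effect on raw code counts.** With the same code rate per answered survey in both groups, the ratio of counts equals the ratio of response rates. Each pair below averages 70%:
- 75% v 65%: 90 / 78 = 1.15.
- 80% v 60%: 96 / 72 = 1.33.
- 90% v 50%: 108 / 60 = 1.80.

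**Step 5. Whether counting participants who ever have the code removes this.** The chance of at least one coded survey is 1 − (1 − q)^k, for code rate q and k answered surveys. At q = 1% and 80% v 60% response:
- 1 − 0.99^96 = 62%.
- 1 − 0.99^72 = 52%.

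It does not, because the count still depends on volume.

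**The case against.** The strongest reply is that the crosstab section never says that cells pool coded segments or that a survey is the unit. Cells could count participants, and a condensed article may leave a software setting to the full plan. Transcripts and survey files are grouped by participant (Qualitative Analysis), and participant summaries are made first (Mixed Methods Integration). Missing-data patterns are examined within and across participants, and compliance will be related to clinical variables. The output is theory refinement and hypotheses, not inferential estimates.

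Most of this stands, and it rules out three stronger readings that a reader might infer:
- **That the crosstabs treat surveys as the unit.** The document does not say so. Only the sample-size sentence in Results counts surveys, and it does not settle how the tables are built.
- **That the comparison has an inflated false-positive rate.** A test on surveys as units would reject in about 39% to 65% of null comparisons at ICC 0.05 to 0.20. As a check, 2 × [1 − Φ(1.96/√design effect)] gives 39%, 52% and 64% at ICC 0.05, 0.10 and 0.20. No test is named for the crosstabs, so these rates describe an analysis that the plan does not specify.
- **That the group above 9% will answer fewer texts.** The Results section expects that group to report lower self-management and device use and higher distress. It says nothing about survey response. Payment is prorated by completion, and everyone must already use CGM regularly. No group-specific rates are given.

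It is also fair that repeated surveys have value: they measure each adolescent's own pattern more precisely. They do not reduce variation between adolescents, which limits a group contrast.

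The reply does not rescue the sample-size sentence, which is wrong as written and is not a detail left to another document. Nor is any of the listed safeguards tied to the crosstabs.

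**Conclusion.** The point holds in two parts of different strength.

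The sample-size statement in Results is incorrect. The between-group sample size is about 15 to 20 participants per group. That supports only large differences, about 0.9 to 1.0 SD of participant-level values at 80% power, two-sided. This rests on the stated enrolment, equal groups and a normal approximation.

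The crosstab comparison is underspecified in a way that matters. Unequal text volume between participants is built into the design, through an optional interview for a subsample and up to 30% of survey data missing, and no adjustment is stated. Whether this biases the HbA1c comparison depends on response or interview share differing by group, which is an assumption. If it does, raw code counts shift by a factor of 1.15 to 1.33 for response gaps of 10 to 20 percentage points, and by 1.80 for a gap of 40.

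**What to change.** 1. In Results, state that the sample size for comparing HbA1c groups is the number of participants, about 15 to 20 per group, and that only differences of about 0.9 to 1.0 SD are detectable at 80% power, two-sided. Say that repeated surveys and interviews add depth per participant.
2. In Mixed Methods Integration, name the participant as the unit in every HbA1c crosstab. For SMS data, give each participant's share of answered surveys that carry the code, averaged within group, alongside the number of participants with the code. The ever-present count should not stand alone, for the reason in Step 5.
3. Tabulate SMS and interview findings separately, with interview tables restricted to those interviewed.
4. Beside each table, show answered surveys and interviews per HbA1c group, so that the reader can judge any volume difference.

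The cost is a change of wording and of table definitions, with no new data collection. The drawbacks are sparser tables and a less favourable sample-size statement.
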